### Follow up

#### Short term follow up

As the primary outcome is birth of a healthy child resulting from a pregnancy that was established in the first 12 months after randomization, each child will be assessed at 6 weeks after the expected day of delivery. For example, a child that is born at a gestational age of 38 weeks will be assessed at 8 weeks after birth, whereas a child born after a gestational age of 30 weeks will be assessed 16 weeks after birth. Parents will be contacted by telephone to enquire on the delivery and the health of the child. When necessary, child health centres and or paediatricians will then be contacted for specific information. All children with severe morbidity will be evaluated and classified by a panel of neonatologists. Detailed information on maternal complication will be obtained from the obstetrician treating the woman concerned.

Certainly not all couples will complete the 12 months of treatment. Drop-outs will largely represent normal patient flow. We aim to keep track of all drop-outs and to document the reason for the drop-out in the database.

#### Long term follow up

We will not be able to follow the children during their lives within the context of this study. However, the health status and subsequent development of children born after IVF and ICSI seems to be comparable to those after spontaneous conception up to the age of 5 years [20]. Furthermore it was recently shown that couples in whom eSET was applied, did not have an unfavourable outcome of their singleton baby when compared to spontaneous singletons [21].

### Outcome measures

#### Primary outcome measure

The primary outcome is the birth of a healthy singleton. A child will be considered healthy when born at term with a normal birth weight, without congenital anomalies [22] and with a normal paediatric examination and development assessment at 6 weeks of age.

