**Methods/Design:**

We plan a multicentre randomised controlled clinical trial in the Netherlands comparing six cycles of intra-uterine insemination with controlled ovarian hyperstimulation or six cycles of Modified Natural Cycle (MNC) IVF or three cycles with IVF-elective Single Embryo Transfer (eSET) plus cryo-cycles within a time frame of 12 months.

Couples with unexplained subfertility or mild male subfertility and a poor prognosis for treatment independent pregnancy will be included. Women with anovulatory cycles, severe endometriosis, double sided tubal pathology or serious endocrine illness will be excluded.

Our primary outcome is the birth of a healthy singleton. Secondary outcomes are multiple pregnancy, treatment costs, and patient experiences in each treatment arm. The analysis will be performed according tot the intention to treat principle. We will test for non-inferiority of the three arms with respect to live birth. As we accept a 12.5% loss in pregnancy rate in one of the two IVF arms to prevent multiple pregnancies, we need 200 couples per arm (600 couples in total).

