#### Secondary outcome measures

Naturally, multiple pregnancy, defined as registered heartbeat of at least two foetuses at 12 weeks of gestation is a secondary outcome. A multiple birth in which al least one of the children has congenital anomalies, will considered as failure of the strategy.

Further secondary outcomes are clinical pregnancy, defined as any registered embryonic heartbeat at sonography; neonatal mortality; pregnancy complications (preterm birth < 37 weeks, birth weight < 2.500 gram, Pregnancy Induced Hypertension (PIH), (pre-) eclampsia, HELLP) costs and patients' preferences.

Patients' preferences are assessed by an (online) questionnaire using a discrete choice experiment (DCE) based on characteristics of both interventions and will be compared with a control group, recruited among women visiting the infertility clinics of the participating hospitals.

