### Analysis

The analysis of all outcomes is on an intention to treat basis. The analysis will be a cost-minimisation when the effectiveness is comparable in all groups. In case of differences in effectiveness a cost-effectiveness study will be performed. Couples will be treated within a time horizon of 12 months

Differences in birth rate per group will be expressed as relative risks with corresponding 95% confidence intervals. A formal test of the difference in pregnancy rate will be performed using chi-square test statistics. Birth rates over time will be compared using life tables.

The medical, economical and social dilemma concerns children with handicaps, which are mostly due to pre-term birth. A literature search will therefore be performed to estimate live-long costs due to handicaps. We will subsequently perform a scenario analysis, in which we will model the costs and effects of the three strategies in this perspective.

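### Other sections define or test the healthy-singleton primary outcome as healthy child, live birth or pregnancy rate, so scoring of healthy multiples and the outcome behind the 12.5-point margin need fixing

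*Protocol article*

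**What the plan says.** The protocol article names the primary or tested outcome in four ways.

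- **Healthy singleton.** The Primary outcome measure section: "The primary outcome is the birth of a healthy singleton". The abstract (Methods/Design) has "Our primary outcome is the birth of a healthy singleton", and the Objective also speaks of a healthy singleton.
- **Healthy child.** Short term follow up: "the primary outcome is birth of a healthy child resulting from a pregnancy that was established in the first 12 months after randomization". The Power calculation also uses a healthy child, at an expected 40% in all three groups.
- **Live birth.** Abstract, Methods/Design: "We will test for non-inferiority of the three arms with respect to live birth".
- **Pregnancy rate.** Analysis: "A formal test of the difference in pregnancy rate will be performed using chi-square test statistics".

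Two further statements bear on multiples. Under Secondary outcome measures: "A multiple birth in which al least one of the children has congenital anomalies, will considered as failure of the strategy". The abstract gives the reason for the margin: "As we accept a 12.5% loss in pregnancy rate in one of the two IVF arms to prevent multiple pregnancies". The Power calculation applies the same 12.5 points to the birth rate of a healthy child.

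**The concern.** The four labels give different numerators. A term twin birth with two healthy children is a non-success as a healthy singleton but a success as a live birth or a pregnancy, and can be read as one under healthy child. The rule on multiple births with an anomaly does not settle this. If every multiple birth already fails, the rule is redundant; if it was meant to add something, the reader is left asking how other multiples are scored.

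The trial exists to reduce multiples, so the versions differ by arm, with most of the difference in IUI-COH. An analyst could choose a version after seeing the data and cite a section for it.

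The margin has a related problem. The abstract presents it as a trade: some pregnancies given up for fewer multiples. On healthy singleton birth the avoided multiples already count in favour of the IVF arms, so using that same margin there credits them a second time.

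**Working it through.** **The plan's own figure.** Non-inferiority, 40% v 40%, margin 0.125, power 80%, one-sided alpha 5%:

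n = (1.645 + 0.842)² × 2 × 0.40 × 0.60 / 0.125² = 190 per group, and 190 / 0.95 = 200.

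This matches. One-sided 2.5% would give 242. The arithmetic is sound; the question is which outcome the 40% and the 12.5 points describe. The 40% equals the IUI-COH cumulative pregnancy rate in the abstract, with multiples not removed.

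**Inputs.**
- IUI-COH: 40% pregnancy, 10% multiple (abstract, Background).
- IVF-eSET: 2-3% multiple (Background section).
- MNC-IVF: four multiple pregnancies are reported (Background section), with no rate, so this arm is not computed.
- Preterm birth in multiples: about 43% (Background section).
- Assumptions: multiple rates are shares of pregnancies, pregnancy rates carry over to births, and every singleton is healthy.

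**Live birth v singleton birth, equal birth rates of 40%.** Singleton rate = birth rate × (1 − multiple share).
- IUI-COH: 0.40 × 0.90 = 36.0%. Multiples are 4 points, or 8 of 200 couples.
- IVF-eSET: 0.40 × 0.98 = 39.2%, to 0.40 × 0.97 = 38.8%. Multiples are 0.8 to 1.2 points, about 2 of 200 couples.
- Shift in the difference: 2.8 to 3.2 points, about 3. As a share of the margin, 3 / 12.5 = 24%.

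**Healthy child v healthy singleton.** If only preterm birth disqualifies a multiple, 57% of multiples remain healthy. At the midpoint of 2.5% multiples, the shift is (4 − 1) × 0.57 = 1.7 points. The other health criteria, such as normal birth weight, would lower it.

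**What a 12.5-point singleton margin tolerates in births.**
- Lowest acceptable IVF singleton rate: 36.0 − 12.5 = 23.5%.
- In births: 23.5 / 0.98 = 24.0%, to 23.5 / 0.97 = 24.2%.
- Tolerated loss from 40%: 16.0 to 15.8 points. For assumed IVF multiple shares of 0 to 5% the range is 16.5 to 15.3.

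**Consequence of restating the planning rate.** At 36% in both arms with the same margin, n = (1.645 + 0.842)² × 2 × 0.36 × 0.64 / 0.125² = 183. On this account alone, 190 remains enough.

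**The case against.** The strongest reply is that the definition is not open. The section reserved for the primary outcome says healthy singleton, and the abstract and Objective agree. That section itself goes on to define when a child is healthy, so healthy child elsewhere may be shorthand. This stands: it is the governing definition, and under it every multiple birth is a non-success. It does not explain live birth as the tested outcome or pregnancy rate in the Analysis section.

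Several stronger readings are tempting, and the document does not support them.

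- *Healthy twins count as successes.* The anomaly rule sits under secondary outcomes and is silent on other multiples. It does not say that only anomalous ones fail.
- *The sponsor ruled out larger pregnancy losses.* The abstract states what loss is accepted; it does not call a larger one unacceptable. The Power calculation puts the margin on healthy-child births.
- *The test's error rate is inflated.* With a true birth loss of exactly 12.5 points (40% v 27.5%) and 190 per arm, the singleton test would declare non-inferiority 16-18% of the time, against 5% for a test on births. That is the chance of passing a singleton test in a scenario set on another outcome. The singleton test keeps its 5% at a true singleton difference of 12.5 points.
- *The 3-point shift holds for both IVF arms.* It is an IVF-eSET figure. That arm also allows two embryos when none is of good quality, so its multiple rate could exceed 2-3%; at an assumed 5% the shift falls to 2.0 points (38.0 − 36.0). The Background section gives the 10% for IUI with or without stimulation.

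The double credit is also conditional. It arises if the abstract's rationale is joined to the singleton outcome, and not if live birth is tested.

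**Conclusion.** The inconsistency is in the text and should be fixed. The article has a governing primary outcome, but its power calculation, non-inferiority statement and formal test are attached to other outcomes, and the anomaly rule leaves the scoring of healthy multiples unclear.

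For IVF-eSET v IUI-COH, live birth against singleton birth moves the difference by about 3 points, a quarter of the margin. Healthy child against healthy singleton moves it by about 1.7 points at most. Applied to singletons, the 12.5-point margin tolerates a loss of about 16 points in pregnancies or births. All three sizes rest on the article's pregnancy and multiple rates carrying over to births; the 3-point and 16-point figures also treat every singleton as healthy. None can be given for MNC-IVF from the article. The shift matters only for a result near the margin, and the sample-size arithmetic is correct, so this is a should-fix point and does not undermine the design.

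**What to change.** Before analysis, by a dated amendment:

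1. Use birth of a healthy singleton as the primary and tested outcome in the abstract and in the Short term follow up, Analysis and Power calculation sections.
2. State that every multiple birth is a non-success for the primary outcome, and reword the anomaly sentence under Secondary outcome measures to match.
3. Restate the planning rate for that outcome: at most about 36% in IUI-COH on the article's figures, and lower once the health criteria are applied.
4. State which outcome the 12.5-point margin applies to. If it is healthy singleton birth, give the reason in terms of that outcome.
5. Also report the non-inferiority comparison on live birth or ongoing pregnancy against the same 12.5 points, so that any loss of pregnancies is visible.

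The cost is a less favourable planning rate, against which the same 12.5 points weigh more heavily (12.5 / 36 = 35% of the reference rate, against 12.5 / 40 = 31%), and one added secondary analysis. Pregnancies, births and multiplicity are already recorded, so no new data are needed.

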#### Secondary outcome measures

Naturally, multiple pregnancy, defined as registered heartbeat of at least two foetuses at 12 weeks of gestation is a secondary outcome. A multiple birth in which al least one of the children has congenital anomalies, will considered as failure of the strategy.

Further secondary outcomes are clinical pregnancy, defined as any registered embryonic heartbeat at sonography; neonatal mortality; pregnancy complications (preterm birth < 37 weeks, birth weight < 2.500 gram, Pregnancy Induced Hypertension (PIH), (pre-) eclampsia, HELLP) costs and patients' preferences.

Patients' preferences are assessed by an (online) questionnaire using a discrete choice experiment (DCE) based on characteristics of both interventions and will be compared with a control group, recruited among women visiting the infertility clinics of the participating hospitals.

### Background and Demographic Characteristics

To assess whether the treatment groups were balanced, the study populations will be compared for baseline measurements including female age, type of infertility (primary/secondary), duration of infertility, intoxications, body mass index, as well as sperm analysis according to WHO standards.

### Analysis

The analysis of all outcomes is on an intention to treat basis. The analysis will be a cost-minimisation when the effectiveness is comparable in all groups. In case of differences in effectiveness a cost-effectiveness study will be performed. Couples will be treated within a time horizon of 12 months

Differences in birth rate per group will be expressed as relative risks with corresponding 95% confidence intervals. A formal test of the difference in pregnancy rate will be performed using chi-square test statistics. Birth rates over time will be compared using life tables.

The medical, economical and social dilemma concerns children with handicaps, which are mostly due to pre-term birth. A literature search will therefore be performed to estimate live-long costs due to handicaps. We will subsequently perform a scenario analysis, in which we will model the costs and effects of the three strategies in this perspective.

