### Economic Evaluation

We plan an economic evaluation alongside the clinical trial. A distinction will be made between costs of medical interventions (direct costs) and costs resulting from productivity losses (indirect or time costs). Standardised unit costs will be calculated for all centres based on actual expenses made during the study. Subsequently, unit costs will be applied to resource use as observed in the participating centres. Resource utilisation will be documented using individual patient data in the case record forms. In addition, each woman will receive questionnaires at 4 weeks, 8 weeks, 12 weeks, 24 weeks, 36 weeks and 48 weeks after treatment start for details on associated direct costs of professional care, and on indirect costs like transportation and productivity loss. Resource unit prices will reflect the unit of staff, materials, equipment, housing, depreciation, and overhead. Productivity loss will be valued using Dutch reference data (handbook of the Dutch health Council). Costs will be presented in Euros.

As the neonatal morbidity and mortality is likely to depend on the number of multiple births, we will perform sensitivity analyses in which we will vary the number of multiple pregnancies in the IUI-COH strategy. Furthermore, sensitivity analyses will be performed on costs, pregnancy rates of the different treatment strategies and the valuation of different outcomes (no child, handicapped child, healthy child).

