### Power calculation

Considering an expected birth rate of a healthy child after 12 months of treatment of 40% in all three treatment groups, with an alpha of 5% and a beta of 20%, 190 patients per group are required to exclude a difference of 12.5% or more to the detriment of MNC-IVF and IVF-eSET. To account for an estimated early drop-out of 5% we will include 200 patients per group.

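### The base-case economic method is chosen by the effectiveness result: cost-minimisation fixes the birth-rate difference at zero in a trial sized only to exclude a 12.5-point loss

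*Protocol article*

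**What the plan says.** The Analysis section sets a two-branch rule for the economic evaluation. The first branch reads "The analysis will be a cost-minimisation when the effectiveness is comparable in all groups"; the second reads "In case of differences in effectiveness a cost-effectiveness study will be performed". The article gives no criterion for choosing between them.

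The Power calculation section assumes an "expected birth rate of a healthy child after 12 months of treatment of 40% in all three treatment groups" and states that "190 patients per group are required to exclude a difference of 12.5% or more to the detriment of MNC-IVF and IVF-eSET", at alpha 5% and beta 20%. It adds: "To account for an estimated early drop-out of 5% we will include 200 patients per group". The Methods/Design part of the abstract describes the margin as an accepted loss: "As we accept a 12.5% loss in pregnancy rate in one of the two IVF arms to prevent multiple pregnancies".

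The Analysis section also plans relative risks with 95% confidence intervals for birth rates, a chi-square test, and a scenario analysis modelling costs and effects in the light of lifelong handicap costs. The Economic Evaluation section plans sensitivity analyses on costs, pregnancy rates and the valuation of outcomes. None of these is conditional on the effectiveness result.

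On cost collection, the Economic Evaluation section takes resource use from case record forms and supplements them with questionnaires covering professional care, transport and productivity loss: "each woman will receive questionnaires at 4 weeks, 8 weeks, 12 weeks, 24 weeks, 36 weeks and 48 weeks after treatment start". Under Follow up, qualifying pregnancies are those established in the first 12 months after randomisation, and each child is assessed 6 weeks after the expected day of delivery.

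**The concern.** Cost-minimisation is valid when effects are known to be equal. Here the label *comparable* would come from a trial of 200 couples per arm, by one of two routes: a non-significant difference, or non-inferiority within 12.5 points. Neither route shows a zero difference. Once the label is applied, the estimated difference in healthy births and its uncertainty drop out of the base case, and the cheapest arm is preferred.

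The main economic conclusion is at stake. The article's Discussion in the abstract looks to the most cost-effective treatment as possible grounds for a worldwide change in first-line practice. Cost-minimisation cannot show how much is saved per healthy birth forgone, so a cheaper arm with somewhat fewer births could be preferred without that trade-off being visible in the base case.

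The questionnaire schedule raises a smaller matter. It runs from treatment start and ends at week 48, whereas conception can occur at any time in the first 12 months after randomisation.

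**Working it through.** **1. The plan's own figure.** Inputs from Power calculation: 40% in every arm, margin 0.125, power 80%. With alpha one-sided 5%:

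n = (1.645 + 0.842)² × 2 × 0.40 × 0.60 / 0.125² = 189.9, rounded up to 190 per group.

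With 5% drop-out, 190 / 0.95 = 200. Both stated figures reproduce. One-sided 2.5% would give 242, so the plan's alpha is one-sided 5%. The sample size is not in question.

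**2. Precision at 200 per arm.** SE = √(2 × 0.24 / 200) = 0.0490. The 95% half-width is 1.96 × 0.0490 = 9.6 points, and the 90% half-width is 1.645 × 0.0490 = 8.1 points.

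**3. How often each route leads to *comparable* when there is a true loss.** Let d be the true loss from 40% and p = 0.40 − d.

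- Non-inferiority, one arm: Φ[(0.125 − d)/SE − 1.645], with SE = √(0.24/200 + p(1 − p)/200). At d = 0.06, SE = 0.0482 and Φ(0.065/0.0482 − 1.645) = Φ(−0.296) = 0.38; simulation gives 0.39.
- Pairwise chi-square, two-sided 5%: the probability of a non-significant result at d = 0.06 is 0.76.

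| True loss | Healthy births lost per 200 couples | Chi-square non-significant (one pair) | Non-inferiority declared (one arm) |
|---|---|---|---|
| 3 points | 6 | 0.91 | 0.62 |
| 5 points | 10 | 0.82 | 0.46 |
| 6 points | 12 | 0.76 | 0.38 to 0.39 |
| 8 points | 16 | 0.62 | 0.24 |
| 12.5 points | 25 | about 0.25 | 0.05 |

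The rule speaks of all groups. With both IVF arms at 34%, simulation gives: non-inferiority for both arms, about 0.24; all three pairwise chi-square tests non-significant, about 0.62; a single three-arm chi-square test non-significant, about 0.77.

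**4. What equality within a tighter margin would need.** With the formula in step 1 and 40% in all arms, n per arm is 297 for 10 points, 464 for 8, 1,188 for 5 and 3,298 for 3, against 200 planned. With no true difference, power at 200 per arm is 82% for 12.5 points, 65% for 10, 50% for 8 and 27% for 5.

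**5. What the base case would hide (assumption only).** The documents give no costs. If an arm saved EUR 500 to 2,000 per couple and lost 6 points, the saving per healthy birth forgone would be 500/0.06 = EUR 8,300 to 2,000/0.06 = EUR 33,300. Whether that is acceptable is a value judgement, and cost-minimisation does not display the figure.

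**6. Questionnaire coverage.** A birth at 40 weeks of gestation falls about 38 weeks after conception, and 48 − 38 = 10. A term birth conceived more than about 10 weeks after treatment start is therefore delivered after the last questionnaire.

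**The case against.** The strongest reply is that the article does not stop at cost-minimisation. Relative risks with confidence intervals are reported whichever branch applies. The scenario analysis and the sensitivity analyses on pregnancy rates and outcome valuation are unconditional. A reader might infer that lost births would appear nowhere; the documents do not support that. What remains is that none of these is a base case built on the observed joint distribution of costs and effects.

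A reader might also infer that the trial can exclude no loss smaller than 12.5 points. That is wrong: with an observed difference of zero, the 95% interval would exclude losses beyond 9.6 points. The trial is simply not sized to exclude smaller losses reliably. Nor does anything show that a loss exists, or that a less effective arm would be cheaper. Both are possibilities that the analysis should be able to display.

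The 76% rests on one reading of *comparable*. Under non-inferiority, the natural reading for this design, the figure is about 39% for one arm and 24% for both. This objection stands, which is why both readings are given. The full protocol may define the term, so its absence from a condensed article is not held against the plan. The switch itself is stated in the article, and either definition leaves the problem in place.

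On questionnaires, a reader might infer that the heavy costs of multiple births are missed. The documents do not support that. Resource use is recorded in case record forms, delivery and child health are ascertained 6 weeks after the expected date, maternal complications come from the obstetrician, and lifelong handicap costs are modelled. Only the questionnaire items are affected.

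**Conclusion.** The point holds for the base-case rule. Followed as written, it sets the birth-rate difference to zero on evidence that cannot establish equality. A possible true loss of 6 points, 12 healthy births per 200 couples, would lead to the cost-minimisation branch with a probability of about 0.24 to 0.77, depending on how *comparable* is read and applied across arms. These figures assume 40% under IUI-COH, 200 analysed per arm, one-sided 5% for non-inferiority and two-sided 5% for chi-square; the figures for all groups further assume the same loss in both IVF arms. The planned supplementary analyses reduce the harm without removing it. The primary clinical comparison and the sample size are unaffected.

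The questionnaire gap is real but secondary. It concerns professional care outside the case record forms, transport and productivity loss around later deliveries. How many births are affected depends on the timing of conception, which the article does not give.

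**What to change.** Delete the conditional rule. State that, whatever the effectiveness test shows, the base case is a cost-effectiveness analysis giving the incremental cost per additional healthy singleton for each IVF arm against IUI-COH. Costs and effects should be estimated together and their joint uncertainty reported, for example by bootstrap with acceptability curves. If the arms prove nearly equal, this analysis will show it, so nothing is lost. Keep the scenario and sensitivity analyses as supplements.

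Add the questions on professional care, transport and productivity loss to the contact already planned 6 weeks after the expected day of delivery.

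The cost is slightly more analysis and a few extra questions at an existing contact. No additional couples are needed.
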